### Secondary outcomes

We will analyze the dichotomous secondary outcomes in the same way. For the continuous secondary outcomes we will calculate the mean difference with 95% confidence intervals, if the data are reasonably normally distributed. Otherwise we will compare the two groups using the median value and assess the role of chance using non-parametric tests.

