## Methods/Design

The primary hypothesis is that MI, locally adapted for glaucoma and its treatment (MIG), increases the uptake of treatment amongst individuals with advanced glaucoma in Bauchi State, Nigeria.

A randomized controlled trial with 1:1 allocation to intervention or no intervention will be used to test this hypothesis.

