Everyone suspected of having glaucoma will be referred to the ophthalmologist (usually [name], but other ophthalmologists will also be trained to detect those who are eligible) for a detailed routine ophthalmic examination. The ophthalmologist will confirm the diagnosis of POAG and determine the treatment of choice based the clinical findings (severity) and socio-economic factors likely to influence adherence to medical treatment (such as education and distance from the hospital). Long-term eye drops will be recommended for those who live near the hospital, are educated and can afford topical medication. These individuals will not be eligible for recruitment. Surgery or laser treatment will be recommended for those with an advanced stage of the disease where this offers the best hope for preventing blindness. These individuals will be potential participants. The ophthalmologist will then explain the disease, the treatment options, and the purpose of treatment, as is standard of care. Participants will choose whether to have laser treatment or surgery. The ophthalmologist will then prescribe eye drops and explain how they are to be used whilst waiting for surgery or laser treatment. Everyone offered surgery or laser treatment will be given a date within one month to re-attend for the procedure. Their name and hospital registration number will be written in the surgical register. They will then be escorted to the project manager for recruitment. Participants wishing to change their date of treatment will be offered a new date, and the surgical register, data record form and spreadsheet will be updated.

The eligibility of each potential participant will be checked by the project manager. All those eligible will be recruited after obtaining written informed consent. If the patient does not consent, reasons will be sought and recorded. After obtaining consent a unique identifier number will be issued. All those recruited will be given a red ID card which contains their name, hospital number and study ID. They will be required to present this card at the registration desk at every visit.

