### Sample size calculation

The sample size is based on the primary outcome and calculated using the SAMPSI command in Stata 12.1 statistical software (StataCorp Texas, USA). Based on the pilot study, we anticipate that 35% of participants in the standard care group will undergo surgery or laser within two months of the date given for the procedure. A sample size of 150 in each arm will be required to detect an acceptance rate of 52.5% (50% relative and 17.5% absolute increase in acceptance) in people in the intervention arm (power 0.8, alpha 0.05). This is based on a calculation of 137 in each arm rounded up to 150 in each arm to allow for loss to follow-up. We believe this absolute increase of 17.5% (corresponding to a relative increase of 50% assuming a 35% acceptance in the control group) would be an important effect to detect. We have also calculated the power of a study of this size to detect differences between the treatment groups with respect to the secondary outcomes. IOP at entry to the study will average approximately 35 mmHg (SD +/- 14 mmHg) (values resulting from the pilot study). Our outcome is based on the final IOP at 12 months. This is likely to be in the order of 25 mmHg in the standard care group. The study will have good power (0.84) to detect differences of 5mmHG or more between the two groups at one year.

We have less information on the probability of losing three or more lines of visual acuity over the year. Figure 
2 shows the proportion of participants losing three or more lines of visual acuity in the standard care group, with power curves for risk ratios of 0.5 and 0.8. It is more likely that we will be able to detect risk ratios in the order of 0.5. The power of the study to detect significant differences using a relative risk of 0.5 is shown in Table 
3.

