### Primary outcome

Our primary outcome is dichotomous (did or did not attend surgery or laser treatment within two months of their scheduled date). Our effect measure will be the risk ratio, that is, we will calculate the proportion of people with this outcome in the intervention group compared to the standard care group. We will report this with 95% confidence intervals. In a trial of 300 people we anticipate that the groups will be fairly well balanced. However, we will also calculate a risk ratio adjusted for factors that may affect uptake of surgery (stage of glaucoma, age, sex, education, and distance from hospital).

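### Final IOP is compared without its entry value, and the choice between means and medians waits for the data: lost precision and an open choice of method, not bias

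*Protocol article*

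**What the plan says.** **IOP and visit counts.** In the Protocol article, Outcomes, the secondary outcomes include mean IOP and mean number of follow-up visits. Sample size calculation adds: "Our outcome is based on the final IOP at 12 months". Data analyses, Secondary outcomes, then states: "For the continuous secondary outcomes we will calculate the mean difference with 95% confidence intervals, if the data are reasonably normally distributed". If the data do not look normal, the arms are compared on medians with non-parametric tests, which are not named. No covariate is mentioned and no rule defines reasonable normality.

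**Entry values.** Sample size calculation gives entry IOP from the pilot as about 35 mmHg, SD 14. The section on data collected at T0 lists clinical findings without naming IOP. Table 2 shows IOP at 6 and 12 months only.

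**Primary outcome.** Besides the plain risk ratio, the plan gives one "adjusted for factors that may affect uptake of surgery (stage of glaucoma, age, sex, education, and distance from hospital"). The procedure chosen is not on that list or among the characteristics to be compared for balance. The choice is made before recruitment and randomisation: "Participants will choose whether to have laser treatment or surgery".

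**The concern.** Entry IOP varies widely and is likely to predict later IOP. Leaving it out makes the confidence interval for the pressure difference wider than it need be, and leaves any chance imbalance in entry IOP uncorrected.

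The switch from means to medians is a separate matter. It changes the quantity being estimated from the one named as the outcome, and it does so after the outcome data have been seen, on a criterion nobody could audit. With 137 to 150 per arm, a confidence interval for a mean difference does not depend on normal data. Visit counts are small whole numbers, so medians can tie while means differ. For the Working Alliance Inventory scores the authors foresaw skew and fixed medians in advance, so the method could be settled here too.

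A lesser matter is the procedure chosen. The pilot findings call laser more acceptable than surgery, so the choice may predict uptake, yet the adjusted risk ratio does not use it.

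**Working it through.** **1. Inputs from the Protocol article**
- Design: "A randomized controlled trial with 1:1 allocation to intervention or no intervention will be used".
- Primary outcome: "we anticipate that 35% of participants in the standard care group will undergo surgery or laser within two months", against 52.5% with the intervention; "power 0.8, alpha 0.05". Sidedness is not stated; two-sided is assumed.
- Size: "This is based on a calculation of 137 in each arm rounded up to 150 in each arm".
- IOP: SD 14 mmHg at entry, difference 5 mmHg, stated power 0.84. No separate SD is given for 12 months, so 14 is used there too.
- Not given: the correlation ρ between entry and 12-month IOP (assumed 0.3 to 0.7), and the share of participants choosing laser (assumed 40% to 75%).

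**2. Reproducing the plan's figures**

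Primary n per arm, with pooled proportion 0.4375: [1.96·√(2·0.4375·0.5625) + 0.842·√(0.35·0.65 + 0.525·0.475)]² / 0.175² gives 125, or 137 with continuity correction. The 137 reproduces.

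IOP power = Φ(5/(14·√(2/n)) − 1.96).
- n = 137: 5/1.69 = 2.96, and Φ(1.00) = 0.840.
- n = 150: 5/1.62 = 3.09, and Φ(1.13) = 0.871.

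The stated 0.84 is therefore that of an unadjusted comparison of final values in 137 per arm. Entry IOP plays no part in it.

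**3. Effect of adjusting for entry IOP, 137 per arm**

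Residual SD = 14·√(1 − ρ²). CI half-width = 1.96·SD·√(2/137). Difference detectable at 80% power = 2.80·SD·√(2/137).

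| ρ (assumed) | Residual SD | 95% CI half-width | Detectable at 80% | Power for 5 mmHg |
|---|---|---|---|---|
| none (plan) | 14.0 | 3.32 | 4.7 | 0.840 |
| 0.3 | 13.4 | 3.16 | 4.5 | 0.873 |
| 0.5 | 12.1 | 2.87 | 4.1 | 0.927 |
| 0.7 | 10.0 | 2.37 | 3.4 | 0.985 |

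At a correlation of only 0.2 the half-width is 3.25 and the power 0.855, a small gain.

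**4. Effect of adding the chosen procedure to the risk ratio**

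Let q be the share choosing laser. Take control uptake as 35% and apply the pilot figure that 75% of those treated had laser. Uptake is then 0.35·0.75/q among laser choosers and 0.35·0.25/(1 − q) among surgery choosers. Assume a risk ratio of 1.5 in both groups and compare the variance of the log risk ratio with and without stratification.

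Example, q = 0.5, n = 137:
- Uptake is 52.5% and 17.5% in control, 78.75% and 26.25% with the intervention.
- Unadjusted variance: 0.65/(137·0.35) + 0.475/(137·0.525) = 0.0202.
- Stratified variance: 0.1969/(137·0.35²) + 0.1805/(137·0.525²) = 0.0165, where 0.1969 and 0.1805 are the average within-group binomial variances.
- Ratio: 0.82.

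| Share choosing laser (assumed) | Control uptake, laser / surgery | Variance ratio |
|---|---|---|
| 40% | 65.6% / 14.6% | 0.63 |
| 50% | 52.5% / 17.5% | 0.82 |
| 60% | 43.8% / 21.9% | 0.93 |
| 70% | 37.5% / 29.2% | 0.99 |
| 75% | 35.0% / 35.0% | 1.00 |

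Forty per cent is about the lowest share these inputs allow, since 1.5·0.656 is already 0.98. The reduction runs from about 37% down to nothing.

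**The case against.** The strongest reply is that nothing here is wrong. Randomisation makes the comparison of final values valid, the text does not forbid adjustment, covariates for secondary outcomes are often left to an analysis plan, and the article is a condensed account. The gain from adjustment rests on a correlation the document does not report. All of that stands, and it limits the weight of the point. It does not answer the switch of method, which the article states itself and which conflicts with its own definition of the outcomes as means.

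Three stronger readings are tempting and are not supported.

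- *The IOP analysis is biased or short of power.* A reader might infer this from the missing covariate. But the stated 0.84 reproduces, and the unadjusted detectable difference at 80% power, 4.7 mmHg, is already below the 5 mmHg aimed for. Whether 5 mmHg is a realistic difference is another question.
- *Adding the chosen procedure would clearly sharpen the primary result.* The pilot gives the laser share only among those treated, so the gain may be nil. The Background figure of fewer than 5% returning for surgery comes from a time without laser and covers everyone offered surgery; it says little about people who prefer surgery when laser is on offer. The covariate would also change only the supplementary adjusted risk ratio, not the plain one.
- *The chosen procedure is already on file.* The T0 list does not name it, and at T1 only the procedure performed is recorded. That exists only for those treated and cannot stand in for the choice.

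**Conclusion.** The point holds as a matter of efficiency and of fixing the method in advance. The plan forgoes precision on IOP that should be available at T0. For assumed correlations of 0.3 to 0.7, the 95% CI half-width would fall by about 0.2 to 0.9 mmHg from 3.3, with no more participants. This assumes that the entry SD of 14 also applies at 12 months, that 137 per arm are evaluable, and that entry IOP is recorded for everyone under clinical findings. The last is a reasonable inference, not an explicit statement.

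The data-driven move from means to medians needs no assumption to establish: the text gives two estimands and no rule for choosing between them. No size can be put on it.

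The chosen procedure is a genuine pre-randomisation variable, but its case is secondary and conditional on its being recorded.

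**What to change.** In Data analyses, Secondary outcomes:

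1. Analyse IOP at 6 and at 12 months as the mean difference adjusted for entry IOP (ANCOVA).
2. Always report the mean difference for IOP and for visit counts, with robust or bootstrap confidence intervals, whatever the distribution looks like.
3. Keep non-parametric tests as sensitivity analyses only, and name them.
4. State in the T0 data list and in Table 2 that entry IOP is recorded.

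Conditionally, if the procedure chosen before randomisation is or can be recorded at T0 for all participants, add it to the balance table and to the supplementary adjusted risk ratio. Do not substitute the procedure performed.

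The first four changes cost only wording and no participants. The conditional one may need one more field on the T0 form. It also requires checking whether the choice can be recovered for those already enrolled (70 by the end of January 2014, under Trial status); the article describes no record that would guarantee this. All changes should be dated before the randomisation code is broken, which the plan ties to completion of the primary analysis.

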### Subgroup analysis

We plan two subgroup analyses of the primary outcome. We will calculate the primary outcome risk ratio and do a test for interaction in the following subgroups: Interviewer A versus interviewer B, and ‘Good’ versus ‘Poor’ sessions according to the MITI scale (see above). We will tabulate reasons for not attending for surgery or laser treatment or follow-up by intervention group and the Morisky adherence scores by intervention group.

Consolidated Standard of Reporting Trials (CONSORT) guidelines will be used when reporting results.

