### Randomization

The randomization list was generated in Excel, using the *rand between* function by [name], away from the project site. Block randomization with a variable block size was used to ensure that the groups will be balanced over time, as the uptake of laser treatment or surgery may fluctuate over time.

The option of MIG or no MIG was printed on headed paper which was signed and stamped. Each was placed in sequentially-numbered opaque envelopes according to the randomization schedule. Each envelope was sealed and stamped. The same was done for randomization to interviewer A or B. These procedures were undertaken in London by persons not involved in the trial.

For each participant, the interviewer in Bauchi will take the next envelope in the sequence and open it to see whether the patient is allocated to MIG or not. They will write the sequence number on the participant’s form and their unique ID number on the outside of the envelope. After returning the letter to the envelope, the envelope will be kept in a sealed, locked container. The same process will be followed for allocation to interviewer A or B.

All participants, whether randomized to MIG or not, will be given an educational graphic leaflet called ‘Silent Thief’ (Additional file
2). All participants will, therefore, receive some additional information about glaucoma and its management.

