### MIG Intervention

Two trained personnel will deliver MIG sessions (Figure 
1).The interview will be conducted in a quiet room within the clinic, in the participant’s preferred language (Hausa or English). Interviewers and participants will be asked to switch off their mobile phones. The participant may be accompanied by someone of their choice.

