### Assessing the quality of the MIG intervention

This will be undertaken in three ways. Firstly, the WAI Short Questionnaire, which is completed by the interviewer and participant immediately after the session, will be used to investigate the relationship between the perceived quality of the interview and trial outcomes (Additional files
3 and
4). Participants who cannot see well, or who cannot read the questionnaire themselves will have the questions read out to them by the other interviewer (to reduce bias). Secondly, a random sample of interviews in English, and translated interview transcripts in Hausa will be sent for independent fidelity testing using the MITI scale, a validated tool used for fidelity testing of MI. Thirdly, taped interviews in Hausa and English will be listened to by [name] and the interviewers on a regular basis throughout the trial as part of supervision sessions, to discuss how well the sessions are going, to identify issues which arise and learning needs, and how interviewing could be improved.

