### Before and after recruitment at T0

Data will be collected for name, age, gender, clinical findings and date given to attend for surgery or laser treatment. For those who refuse, reasons for not agreeing to participate will be sought. For those who agree, contact details will be recorded: detailed address; telephone numbers of individual/family/neighbor; sociodemographic data and randomization sequence number. All data will be entered into a customized, password protected database on the day of recruitment. The form will be kept in a lockable cupboard only accessible to the project manager in an office dedicated to the trial, which is locked when not in use.

For those allocated to MIG the interview will be conducted at T0. If a second MI session is indicated, the reason for this will be recorded. After every interview, WAI questionnaires will be completed independently by the participant and the interviewer. These forms will be kept in a lockable cupboard in a separate office dedicated to the MIG interviews. This office will be locked at all times when not in use for MIG sessions. The project manager and ophthalmologist will not have access to these forms at any time. Data from these forms will be entered into a separate password protected database.

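### The two planned subgroup interaction tests rest on session features that standard-care participants lack (MITI quality) or are not said to have (interviewer), so both should be restated as comparisons within the MIG arm

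*Protocol article*

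**What the plan says.** The Subgroup analysis section names two analyses of the primary outcome. For each it will give the risk ratio and "do a test for interaction in the following subgroups: Interviewer A versus interviewer B", the second factor being good versus poor "sessions according to the MITI scale (see above").

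The Primary outcome section under Data analyses defines that risk ratio: "we will calculate the proportion of people with this outcome in the intervention group compared to the standard care group".

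On who has an interviewer and a session:
- MIG Intervention: "Two trained personnel will deliver MIG sessions".
- Before and after recruitment at T0: "For those allocated to MIG the interview will be conducted at T0".
- Randomization, on the envelopes prepared in London: "The same was done for randomization to interviewer A or B". On their use in the clinic: "The same process will be followed for allocation to interviewer A or B".

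On who has a MITI score, Assessing the quality of the MIG intervention says that "a random sample of interviews in English, and translated interview transcripts in Hausa will be sent for independent fidelity testing". The size of that sample is not given.

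**The concern.** A test for interaction asks whether the effect of MIG against standard care differs between levels of a factor. It needs participants at each level in both arms. Someone in standard care has no session, so has no MITI rating and has been interviewed by nobody.

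Two things are at stake. First, a difference in uptake between good and poor sessions could be presented as modification of a randomised effect, when it is an association within one arm. Second, the interviewer question, which the design can answer by randomisation, could be answered with an unsuitable standard error and lose power that it can ill afford.

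**Working it through.** **Inputs.** Uptake of 35% in standard care and 52.5% with MIG, and 150 per arm (Sample size calculation). An equal split of 75 per interviewer is my assumption.

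**The plan's own figure.** None is given for the subgroup analyses. The nearest is 137 per arm, which confirms how the two rates are used. With difference 0.175 and mean rate 0.4375, two-sided alpha 0.05 and power 0.8:

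n = [1.960·√(2·0.4375·0.5625) + 0.842·√(0.35·0.65 + 0.525·0.475)]² / 0.175² = 124.96

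The continuity correction gives (n/4)·[1 + √(1 + 4/(0.175n))]² = 136.1, rounded up to 137. It reproduces.

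**Can the interaction be estimated?** Take a model with an intercept, arm, interviewer B, and arm × interviewer B. If controls have no interviewer, the last two columns are identical, so the design matrix has rank 3 of 4. The same holds with good or poor session in place of interviewer. The rank reaches 4 only if controls also carry the label.

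**What a shared control group yields.** With uptake pA, pB and pc, the ratio of the two risk ratios is (pA/pc)/(pB/pc) = pA/pB. The control rate cancels, leaving a comparison within MIG.

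**Standard errors, interviewer.** The variance of log p is (1−p)/(np), evaluated with both interviewers at 52.5%:
- MIG, per interviewer: 0.475/(75·0.525) = 0.01206
- all controls: 0.65/(150·0.35) = 0.01238
- half the controls: 0.65/(75·0.35) = 0.02476

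| Analysis of log(pA/pB), or of the log ratio of risk ratios | SE | Relative to direct |
|---|---|---|
| A v B within MIG: √(2·0.01206) | 0.155 | 1 |
| Shared controls, risk ratios wrongly taken as independent: √(2·0.01206 + 2·0.01238) | 0.221 | 1.42 |
| Controls genuinely labelled and split 75/75: √(2·0.01206 + 2·0.02476) | 0.271 | 1.75 |

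In the second row the control variance is counted twice although it cancels, so the SE is wrong. The real size of a nominal 5% test is 2·[1 − Φ(1.96·1.42)] ≈ 0.005. In the third row the two risk ratios really are independent, so that SE is right for that estimator and the test keeps its 5% size. The factor 1.75 measures efficiency lost against the direct comparison.

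**Power on the log scale**, with assumed gaps centred on 52.5%:

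| Gap between interviewers | Direct | Shared controls taken as independent | Labelled controls |
|---|---|---|---|
| 20 points (62.5% v 42.5%) | 0.67 | 0.36 | 0.29 |
| 10 points (57.5% v 47.5%) | 0.23 | 0.06 | 0.10 |

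The direct comparison reaches roughly 80% power only at a gap of about 23 points.

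**MITI quality.** No power can be computed, because the number of scored sessions is not stated. The article itself points to confounding. The Discussion expects English-speaking participants to be better educated and more aware of glaucoma, and says that transcripts lose tone of voice and pauses. The Primary outcome analysis lists education among the factors that may affect uptake. Language and education could therefore relate both to the MITI rating and to uptake.

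**The case against.** **Controls may carry an interviewer label.** The Randomization section describes envelope opening for each participant and then says that the same process is followed for interviewer. That can be read as everyone drawing an interviewer envelope, and the flow chart is not shown. This stands as an uncertainty. A reader might infer that the interviewer factor is certainly confined to the MIG arm, but the text does not settle it. The natural reading is that it is confined, since interviewers deliver only MIG sessions and no section gives controls a label. If controls are labelled, the test is valid. The label is then inert in controls and adds only noise. None of this helps the MITI analysis.

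**The wrong standard error is not in the text.** The article does not say that the two risk ratios will be treated as independent. One model with three levels (control, A, B) and an A-to-B contrast gives the correct SE, and such detail may sit in an analysis plan not shown. This stands. The 1.42 and 0.5% figures describe one possible implementation, whose error would be conservative. A reader might also take the 1.75 ratio as a second miscalculated SE, but that SE is correct for its estimator.

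**The authors already caution on subgroups.** The Discussion says that subgroup analyses may lack power. That concerns precision. A larger sample would not supply the missing comparator.

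**The language problem is acknowledged.** The Discussion notes possible bias from assessing English interviews alone and arranges for translated transcripts. This helps coverage, but good versus poor remains a non-randomised contrast.

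**Conclusion.** The point holds fully for MITI quality: the factor is measured after randomisation, in one arm only and on a sample, so the stated interaction cannot be estimated. What remains is an association open to confounding.

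For interviewer it holds on the natural reading of the article. The question itself is sound because interviewer is randomised; only the stated analysis is unsuitable. The consequence ranges from none (a three-level model contrasting A with B), through a valid but inefficient test (labelled controls, SE 1.75 times that of the direct comparison), to a test running at about 0.5% instead of 5% (shared controls treated as independent, SE 1.42 times the correct one). These sizes assume 75 per interviewer and the planning rates.

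A reader might infer that the trial's main conclusion is at risk. It is not: the primary risk ratio, its adjusted version, the intention-to-treat comparison and the sample size are untouched. This should be fixed, but it is a correction to two secondary analyses.

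**What to change.** Reword the Subgroup analysis section:
1. Delete the test for interaction for both factors.
2. Compare interviewer A with interviewer B within the MIG arm, by allocated interviewer, as a randomised comparison: risk ratio with 95% confidence interval. State whether standard-care participants draw an interviewer envelope.
3. Report MITI quality against uptake among scored MIG sessions only, labelled exploratory and observational, adjusted for education and, where recorded, session language. Give the number of sessions scored.

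The cost is wording only; no new participants or visits are needed. Education is already planned for collection. Session language is not named in the article's list of data at T0 and the data forms are not shown, so that adjustment depends on its having been recorded.
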